### Secondary outcome

The secondary outcomes include the individual components of the primary outcome, a composite endpoint of unstable angina and other hospitalisations for cardiac reasons and angina frequency and stability, physical limitations, treatment satisfaction and quality of life. In the RCT the cost-effectiveness, the proportion of ICA procedures not performed owing to the availability of FFR-CT and the proportion of invasive FFR measurements avoided by the use of QFR will be assessed.

### Study procedures

#### Registry

The registry includes patients with CAD-RADS 0–2 and 5. These patients will be treated as determined by the referring physician team and includes guideline conformant optimal medical therapy (OMT). After inclusion, patients in the usual care arm will not undergo any additional invasive tests or procedures.

#### Randomisation arm FFR-CT

The CCTA of patients randomised to the FFR-CT arm will be analysed by HeartFlow FFR-CT (HeartFlow, Mountain View, CA, USA). Participating hospitals will follow local CCTA scanning protocols consistent with quality standards as defined by the Society of Cardiovascular Computed Tomography [5]. Prior to the FFR-CT analyses, the quality of CT images will be evaluated by the local radiologist and quantitatively scored for all vessel segments ≥ 2 mm in diameter to select cases appropriate for FFR-CT analysis.

FFR-CT analyses will be performed on the resting CCTA images using the HeartFlow Core Lab. It is expected that the CCTA of 10–15% of the enrolled subjects will be of acceptable quality [6, 7]. Haemodynamically significant CAD will be defined as FFR-CT ≤ 0.80 in any segment distal from a coronary stenosis with a reference size of ≥ 2.0 mm. If haemodynamically significant CAD is present in a segment suitable for revascularisation, these patients will be referred for ICA and undergo revascularisation. Patients with FFR-CT values > 0.80 in all segments will not be referred for ICA and will receive OMT.

#### Randomisation arm QFR

Patients randomised to the QFR arm will undergo ICA to visualise the coronary arteries. The diagnostic ICA will be performed by certified interventional cardiologists using imaging standards defined by the ACC/AHA Task Force on Practice Guidelines and the Society for Cardiac Angiography and Interventions. QFR will be estimated in the catheterisation laboratory immediately after injection of contrast if there is at least one lesion with a diameter stenosis between 30% and 90% in a vessel with reference size ≥ 2.0 mm. QFR will be calculated using the QAngio XA 3D/QFR analytical software solution (Medis Medical Imaging Systems, Leiden, The Netherlands). To obtain a QFR measurement, two angiographic views of the vessel of interest at least 25° apart are obtained on the least foreshortening of the stenosis and a minimum overlap between the main vessels and side branches. Haemodynamically significant CAD is defined as QFR ≤ 0.80. QFR will be performed on-site by QFR-certified observers. It is expected that in 1–6% of enrolled patients the angiographic views will not fulfil the above criteria and that QFR can therefore not be performed [8–10].

#### Randomisation arm standard of care

Patients randomised to the usual care arm will, in cases with an intermediate severity stenosis (50–90% diameter stenosis) that can be safely measured by invasive means, undergo ICA and invasive pressure measurements in accordance with the ESC guidelines. The management strategy (percutaneous coronary intervention or coronary artery bypass graft or OMT) will be determined based on this information. Haemodynamically significant CAD is defined as FFR ≤ 0.80 and instantaneous wave-free ratio and resting full-cycle ratio ≤ 0.89.

#### Study endpoints and questionnaires

Clinical endpoints, mortality and MACE will be obtained from the electronic patient records and other data sources (general practitioner, national death registry and participants themselves) until the end of the study (at least 12 months’ follow-up for each participant, maximum follow-up 30 months). A blinded clinical endpoint committee will adjudicate all endpoints.

Symptoms of angina are recorded by use of the Seattle Angina Pectoris Questionnaire and mental status is assessed using PHQ‑9. Medical costs and productivity losses are recorded using the iMTA Medical Consumption Questionnaire and iMTA Productivity Cost Questionnaire (iMTA, Rotterdam, The Netherlands). Health-related quality of life, as measured by the Patient-Reported Outcome Measurement Information System (PROMIS-10), including the score on the European Quality of Life 5 Dimensions 5 Levels questionnaire (EQ-5D-5L; EuroQol, Rotterdam, The Netherlands), will be established at baseline and 1, 3, 6 and 12 months after inclusion. In addition, patients will be asked to complete a test rating scale for discomfort and satisfaction with the testing procedure. Patients who receive an invasive pressure measurement after the FFR-CT or QFR test will be asked to compare the tests directly.

### Statistical considerations

All analyses will be done according to the intention-to-treat principle defined as all subjects randomised into the trial. Treatment classification will be based on the result of the randomly allocated diagnostic test. The per-protocol population will be defined as all subjects randomised into the trial receiving their assigned randomised treatment.

#### Sample size

The sample size calculation is based on the expected percentage of patients with the primary composite endpoint of MACE at 12 months. A 3.7% incidence in the FFR-guided arm and a non-inferiority margin of 5% are assumed based on the results of the MR-INFORM trial [11]. With these assumptions, a sample size of 221 patients in each arm is estimated to determine non-inferiority (one-sided level of significance of 0.025) and to provide the trial with at least 80% power. Based on local experience approximately 25% of the patients evaluated by CCTA have a CAD-RADS score of 3 or 4A. The pertinent literature suggests that a maximum of 15% of the patients are not suitable for FFR-CT or QFR analyses [8, 9, 12–14]. Allowing for an exclusion percentage of 15% and a dropout rate caused by loss to follow-up of 5%, a total sample size of 3300 patients is required. It should be noted that 75% of these patients are asked for follow-up only (CAD-RADS 0–2), and 25% (*n* = 825) will be randomised to the different techniques to measure FFR.

#### Data analyses

The primary endpoint will be assessed in a non-inferiority analysis of the FFR-CT-guided group and the QFR-guided group compared to the conventional strategy-guided group. The null hypothesis is that the MACE incidence rates of both FFR-CT and QFR are equal to or lower than the incidence rates of the usual care arm within the non-inferiority margin of 5%. If non-inferiority is confirmed, superiority will be assessed. Differences in the primary outcome will be assessed graphically using Kaplan-Meier curves and tested with the log-rank test as recommended for an analytical approach to a three-arm non-inferiority trial [15]. In addition, analysis considering crossovers will be performed. No formal interim analysis for efficacy is planned for this study.

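### The null hypothesis of the primary analysis is the non-inferiority claim itself, so null and alternative are transposed

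*Protocol article*

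**What the plan says.** Under Data analyses, the protocol article states the primary hypothesis: "The null hypothesis is that the MACE incidence rates of both FFR-CT and QFR are equal to or lower than the incidence rates". The comparator is usual care, and the sentence closes by allowing for the 5% margin. The article then adds: "If non-inferiority is confirmed, superiority will be assessed". The test it names is Kaplan-Meier curves with differences "tested with the log-rank test as recommended for an analytical approach to a three-arm non-inferiority trial".

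Under Sample size, "A 3.7% incidence in the FFR-guided arm and a non-inferiority margin of 5% are assumed", and 221 patients per arm are calculated "to determine non-inferiority (one-sided level of significance of 0.025") and "to provide the trial with at least 80% power". Allowances for unsuitable images and loss to follow-up bring the randomised total to 825.

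The article nowhere else states the hypotheses, and it gives no rejection rule or confidence limit.

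**The concern.** Let d be the MACE risk on FFR-CT or QFR minus the risk in usual care. The printed null is d ≤ 5 points, which is exactly the non-inferiority region. A non-inferiority test has to start from the opposite position (d ≥ 5 points) and reject it.

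The direction of the null determines which error the 0.025 level limits. Under the conventional null it limits the risk of calling a strategy non-inferior when its excess is 5 points or more. Under the printed null it limits the risk of calling an acceptable strategy inferior, and the first risk is left uncontrolled. Success would then mean failing to reject, which becomes more likely as the trial gets smaller or noisier. The endpoint includes death and myocardial infarction, so the uncontrolled error is the one that matters most.

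**Working it through.** **Inputs (Sample size section).** Usual-care MACE 3.7% at 12 months; margin 5%, read as absolute percentage points; one-sided 0.025; power 80%; 221 per arm. Test-arm rates above 3.7% are illustrative.

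**1. Which null does the sample size use?** With both true rates at 3.7% and the null d ≥ 0.05:

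n per arm = (1.960 + 0.842)² × 2 × 0.037 × 0.963 / 0.05² = 7.849 × 0.07126 / 0.0025 ≈ 224.

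The article gives 221. At 221, SE = √(0.07126/221) = 0.01796 and power = Φ(0.05/0.01796 − 1.960) = Φ(0.824) = 79.5%. The stated figure therefore reproduces closely under the conventional null.

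**2. What follows from the printed null?** Suppose non-inferiority is declared unless d ≤ 0.05 is rejected at one-sided 0.025. With p the true test-arm rate and SE = √[(0.037 × 0.963 + p(1 − p))/221]:

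- P(declared, printed null) = Φ(1.960 − (d − 0.05)/SE)
- P(declared, conventional null) = Φ((0.05 − d)/SE − 1.960)

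| True test-arm rate | d | SE | Printed null | Conventional null |
|---|---|---|---|---|
| 8.7% | 5.0 points | 0.0228 | 97.5% | 2.5% |
| 10% | 6.3 points | 0.0238 | 92.1% | 0.6% |
| 12% | 8.3 points | 0.0253 | 74.4% | 0.05% |
| 13.7% | 10.0 points | 0.0264 | 52.6% | 0.01% |

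Simulation with 400,000 replicates and Wald intervals agrees. At 8.7% it gives 98.0% (printed) and 3.2% (conventional); at 13.7% the printed null gives 52.7%.

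**3. Effect of sample size.** At a 10-point excess, the printed-null rule declares non-inferiority 85.5% of the time with 50 per arm, 52.6% with 221 and 43.9% with 275. The smaller the trial, the more often it succeeds.

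**4. The test that is named.** No margin shift is stated for the log-rank test; the ordinary version tests equality of the curves. If non-significance in such a test at one-sided 0.025 were taken as confirmation, a normal approximation for proportions gives P(declared) = Φ(1.960 − d/SE) at 221 per arm: about 41% at 8.7%, 25% at 10% and 9% at 12%. These are lower than in the table but still far above 2.5%.

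**The case against.** The strongest reply is that this is a slip of wording. No sentence says that non-inferiority is concluded by failing to reject; the article speaks of non-inferiority being confirmed, which suggests a positive demonstration, and the sample size was plainly built on the conventional null. On this view the printed null mislabels the working hypothesis and nothing in the design is affected. Much of that stands: the intent can probably be recovered, and correcting the sentence reconciles the two sections. But the sentence has no valid reading as a non-inferiority null, because the margin clause places the whole acceptable region inside it.

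The second reply is that the 97.5%, 92% and 74% figures assume a margin-shifted test that the article does not name. This is fair. They show what the printed null implies when tested on its own terms, and step 4 of the working gives the lower figures for an ordinary equality test. Neither rule comes close to 2.5% at the margin.

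The third is that an intention-to-treat analysis would include about 275 per arm (825/3, assuming equal allocation), not 221. The probabilities then become about 91% at 10% and 69% at 12%, and remain 97.5% at the margin.

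Finally, this is a condensed article, and a decision rule may sit in the full protocol or analysis plan. Its absence here is therefore not the fault. The fault is that the article states its primary hypothesis and states it the wrong way round.

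**Conclusion.** The concern holds. The null under Data analyses is the non-inferiority region, and the sample size rests on the opposite null, so the 0.025 level cannot do the work that both sections assign to it. Followed literally, the chance of declaring non-inferiority at a true excess of exactly 5 points is 97.5%, where 2.5% is intended.

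This size rests on an absolute margin, 3.7% MACE in usual care, 221 per arm, a normal approximation, and non-rejection being taken as success. The likely explanation is a drafting error. It still has to be corrected, because this sentence defines what the trial's type I error protects against and the article contains no decision rule that would override it.

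**What to change.** Replace the sentence with two hypothesis pairs, one for each strategy:

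- FFR-CT: H0: p(FFR-CT) − p(usual care) ≥ 5 percentage points; H1: the difference is < 5 points.
- QFR: H0: p(QFR) − p(usual care) ≥ 5 percentage points; H1: the difference is < 5 points.

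Declare non-inferiority for a strategy only if the upper one-sided 97.5% confidence limit for its 12-month difference (equivalently, the upper limit of the two-sided 95% interval) is below 5 points. Separate pairs also fit the article's Conclusion and Summary, which allow either strategy to succeed on its own; the printed null covers both together.

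State in the same place that an ordinary log-rank test does not decide non-inferiority, so that the named test and the confidence-limit rule do not compete.

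The cost is about two sentences in the protocol and analysis plan, to be settled before any unblinded analysis. Margin, significance level, endpoint and sample size are unchanged. Under the corrected null, power is 79.5% at 221 per arm and 87.4% at 275.

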### Ethical considerations

This study will be conducted according to the principles of the Declaration of Helsinki and in accordance with the most recent European Good Clinical Practice rules and the ISO 14155:2020. Major adverse events will be reported to the Data Safety Monitoring Board (DSMB) and the accredited medical research ethics committee. The DSMB reviews adverse event data, other safety data, quality and completeness of study data, and enrolment data to ensure proper trial conduct.

### Funding, trial registration and time line

The iCORONARY trial is registered on ClinicalTrials.gov (NCT04939207). The trial was initiated as a collaboration between St Antonius Hospital and University Medical Centre Utrecht, and more than eight Dutch centres are anticipated to include patients. The iCORONARY trial is funded by the Dutch Organization for Health Research and Development (ZonMW) and the health insurance companies in the Netherlands (grant number: 852002131), none of which are involved in trial design and processes.

Initial recruitment at the St Antonius Hospital began in March 2022. The trial will continue until 3300 patients are included and followed for 12 months.

## Summary

The iCORONARY trial is a multicentre, prospective, randomised controlled, non-inferiority trial that assesses whether a non-invasive or less-invasive strategy for FFR-CT or QFR is non-inferior to invasive angiography and FFR measurements in guiding the need for revascularisation in patients with stable CAD. Non-inferiority of FFR-CT and/or QFR to the current standard of care would establish those procedures as an attractive, cost-effective, non-invasive or less invasive alternative to current diagnostic pathways. The results of the iCORONARY trial might contribute to the guidelines on diagnosis and management of stable CAD.
